# The effectiveness of Multidimensional Treatment Foster Care for Preschoolers (MTFC-P) for young children with severe behavioral disturbances: study protocol for a randomized controlled trial

**DOI:** 10.1186/1745-6215-14-197

**Published:** 2013-07-05

**Keywords:** Attachment, Autonomic reactivity, Behavior, Cortisol, Foster care, Preschool children

## Abstract

**Background:**

Among children placed out of home, behavioral and relationship functioning is often problematic. When placed in foster care, problems tend to persist or even worsen and increase the risk of placement breakdown. Multidimensional Treatment Foster Care for Preschoolers is an intensive behavior-focused program for young foster children (3 to 7 years) aiming to provide children with a positive and stimulating foster family setting and individually tailored behavioral interventions. This study will be the first to examine the effectiveness of Multidimensional Treatment Foster Care for Preschoolers outside the US and to examine the effectiveness across a broader range of problems related to foster care.

**Methods:**

This is a randomized controlled trial, wherein we expect to include 80 child-foster carer dyads. Forty dyads will be assigned to Multidimensional Treatment Foster Care for Preschoolers and 40 to treatment as usual, following pre-randomization. Data to be gathered concern problem behavior, symptoms of attachment disorder, post-traumatic stress symptoms, quality of life, hypothalamic-adrenal-pituitary axis functioning, parental stress and autonomic reactivity, to be collected via questionnaires, observations, interviews, saliva and recording at six time-points over 24 months. To compare treatment outcomes, Fisher’s exact tests and repeated measures (mixed models) and independent t-tests will be used. All analyses will be performed following the intention-to-treat principle.

**Discussion:**

Examining the generalizability of previous findings in the US and extending these previous findings is a step towards improving knowledge about treatment of young foster children with severe behavioral, emotional and attachment problems.

**Trial registration:**

NTR1747

## Background

The large proportion of young children in the foster care population is of concern, with children younger than five years old representing over a third of foster children in the US (33% of 400,540 [1]) and the Netherlands (36% of 8,944 [2]). Children often enter foster care after serious neglect and abuse. Among foster children, there is wide variation in behavioral and relationship functioning, which is on average more problematic compared with that of children living with biological parents [3-5]. Foster children often suffer from post-traumatic stress disorder [6] as well as more complex traumatic symptoms [7], more disorganized attachment [8], and high frequencies of clinical symptoms of disturbed attachment [9-11]. Additionally, adverse or inconsistent caregiving tends to cause atypical functioning of children’s biological stress systems, such as changes in the hypothalamic-adrenal-pituitary (HPA) axis, represented by abnormal cortisol segregation [12,13], and altered stress regulation activity of the autonomic nervous system (ANS) [14]. After placement in foster care, problems tend to persist or even worsen [15,16], and not only negatively affect the parenting behavior of foster carers [17] but also increase the risk of placement breakdown. Placement breakdown may start a vicious circle in which the chance of another failure increases with every breakdown [18]. The last alternative is often residential placement, which fails to provide opportunities for developing attachment [19], causes developmental delays [20], and places children at further risk. To prevent foster children from further problems, these children are in need of evidence-based programs that combine foster placement with effective treatment of emotional and behavioral disorders and parental stress. Multidimensional Treatment Foster Care for Preschoolers (MTFC-P) tends to address these needs, providing a positive and stimulating foster family setting for these children. Foster caregivers are taught effective behavioral management strategies and children receive individually tailored behavioral interventions. Dozier and Rutter [21] suggested that when foster carers and children gain control over behavioral problems, the potential for the development of a (secure) attachment relationship increase. The absence of behavioral problems results in less parental stress for the foster carers, allowing them to better respond to the child in a sensitive and nurturing way - supporting children’s belief in the caregiver’s availability. With the increase of (secure) attachment behaviors, the risk of disturbed attachment declines, because behaviors of either type are theoretically incompatible with one other [11,19].

Previous studies in the US have shown that, relative to children in regular foster care, children in MTFC had fewer placement failures [22], improved HPA axis functioning [23], increased secure attachment behavior and less resistant behavior [24]. Although MTFC-P is quite successful in the US and transportability of the MTFC model for older children has been shown in a Swedish context [25], the efficacy of the preschool version has not been replicated in other countries where implementation challenges and cultural differences may play a role. Outside the US, in the Netherlands, only a small pilot study was conducted, preliminary to this study. Early findings suggested less problem behavior in the MTFC-P intervention [26].

This protocol is for a study intending to examine whether US findings regarding MTFC-P also apply for children in foster care in the Netherlands. The study also aims to extend on previous studies by examining the effects of MTFC-P on post-traumatic stress symptomatology, symptoms of attachment disorder and quality of life. With the present study, we compare the effects of MTFC-P with a treatment as usual (TAU) for foster children at risk for placement breakdown. We hypothesize that MTFC-P is more effective than TAU for young foster children with emotional and behavioral disorders. Effectiveness is measured in terms of decreased problem behavior; fewer symptoms of disturbed attachment; fewer severe post-traumatic stress symptoms; improved quality of life; recovery of HPA-axis functioning, indicated by recovery of atypical cortisol activity; and less parental stress. We expect that, relative to control children, at the end of the treatment children in the MTFC-P group will show less maladaptive responses of the ANS, indicated by heart rate, respiratory sinus arrhythmia and pre-ejection period, to separation and reunion with caregivers and strangers.

## Methods

### Participants

Eligible participants are children between 3 and 7 years, referred to our department of Treatment Foster Care at De Bascule, Academic Center for Child and Adolescent Psychiatry (Amsterdam, Netherlands). Eighty child-foster carer dyads will be included in the study.

### Inclusion criteria

The inclusion criteria for children and foster carers are to meet the eligibility criteria of MTFC-P. Children are eligible if they are between 3 and 7 years of age and indicated for permanent foster care placement.

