### Primary objectives

#### Problem behavior

The Child Behavioral Checklist for ages 1.5 to 5 (CBCL 1.5-5 [29]) and 6 to 18 (CBCL 6–18 [30]) assesses the internalizing and externalizing behaviors of children. The CBCL is completed by foster parents and consists of hundred (ages 1.5-5), respectively 113 (ages 6–18) items. Items are rated on a 3-point scale (*0 = not at all true, 1 = somewhat true, 2 = very true*). A Dutch translation of the CBCL is used. Prior studies in Dutch populations revealed satisfactory reliability and validity of the CBCL 1.5-5 and 6–18 [31,32]. Preliminary analyses based on data from the present study revealed good internal consistency with alphas >0.80 for all scales except for internalizing problems (alpha = 0.60).

The Teacher Report Form for ages 1.5 to 5 (TRF 1.5-5 [29]) and 6 to 18 (TRF 6–18 [30]) assesses children’s school functioning and behavioral problems. The TRF is completed by foster parents and consists of hundred (ages 1.5-5), respectively 113 (ages 6–18) items. Items are rated on a 3-point scale (*0 = not at all true, 1 = somewhat true, 2 = very true*). Depending on the age of study children, daycare providers or teachers complete this questionnaire. Preliminary analyses based on data from the present study revealed good internal consistency with alphas >0.80 for all scales except for internalizing problems (alpha = 0.44) and externalizing problems (alpha = 0.58). A Dutch translation of the TRF is used. Psychometric properties have been found to be adequate in Dutch populations [33].

The Strengths and Difficulties Questionnaire (SDQ [34]) is a behavioral screening instrument, completed by (foster) parents. This questionnaire consists of 25 items, rated on a three point scale (0 = not true, 1 = somewhat true, 2 = very true) testing children’s psychological attribution to five subscales and one total scale (alphas given in parentheses): emotional problems (0.65), conduct problems (0.68), hyperactivity (0.77), peer relations (0.57), prosocial behavior (0.73) and total difficulties (0.67). Alphas were based on preliminary data from the present study. We use a Dutch translated version of the SDQ. Reliability and validity of the SDQ-parent report in a Dutch sample have been found to be satisfactory [35].

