#### Data collection

Data is collected at six time-points over 24 months: T(1) at start, T(2) 3 months after start, T(3) 6 months after start, T(4) 9 months after start (end of treatment), T(5) 12 months after start and T(6) 24 months after start. Parents and teachers are asked to fill out the questionnaires at all six measurements occasions. Questionnaires are sent to their homes, but when necessary researchers will help them filling out the questionnaires by telephone or face-to-face. The DAI interview is administered by telephone at T(2) and T(4) by a trained interviewer. Saliva is collected at T(2), T(3) and T(4) on five consecutive days, three times a day (see Measures). During the saliva collection, foster carers are called everyday to complete the PDR. The Strange Situation Procedure and accompanying VU-AMS measure is scheduled one week before the end of the treatment (see Table 2).

**Table 2 T2:** Research procedure

**Study phase**	**Time-point**	**Time after start**	**Action**
**Recruitment**			Assess for eligibility
			Randomization
			Send information
			Complete informed consent^a^
**Treatment**	T(1)	6 weeks	Questionnaires
	T(2)	3 months	Questionnaires, interview, saliva collection
	T(3)	6 months	Questionnaires, saliva collection
	T(4)	9 months	Questionnaires, interview, saliva collection, observation, autonomic nervous system recording
**Follow-up**	T(5)	12 months	Questionnaires
	T(6)	24 months	Questionnaires

^a^ No consent – child randomized to treatment as usual.

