#### Planned statistical analyses

Analyses are performed using the software package SPSS (Statistical Package for the Social Sciences), version 17.0. Fisher’s exact tests are used for the categorical data, effect sizes are estimated by the relative risks, absolute risks and relative risk reduction. Effect parameters are presented within a 95% confidence interval. The continuous measures are analyzed with repeated measures (mixed models) and independent t-tests. Effect sizes are indicated by partial eta squared and Cohen’s d. Primary analyses are performed following the intention-to-treat principle. However, we will also perform a ‘treatment received’ analysis and a separate comparison of children whose parents refused participation and who received TAU after randomization to MTFC-P. Depending on the amount and type of data missing we will explore possibilities to deal with missing data, but we plan to use mixed models.

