A second limitation to our RCT is the lack of an adequate baseline measure. Because children are new in the foster family at the start of the intervention, we decided to postpone the first assessment. A new placement is often accompanied by a temporary increase or decrease in problems, and foster carers and children have just met. Adhering to a randomized trial will minimize baseline differences between children in the two conditions. A third limitation is that foster parent’s perception of children’s behavior is one of the primary focuses of the treatment, but also a primary objective of the present study. We attempt to limit the effect of reactive measures by the inclusion of teachers’ perceptions of children’s behavior. In addition, we inserted the Strange Situation Procedure. Although this observation of attachment is only post-treatment, we expect that the random allocation will diminish selection bias. Other alternatives have been considered, such as observational measures of children’s behavior, but their benefits are not expected to compensate for the extra burden they would place on participants. If we are able to meet the challenges and include sufficient participants, we will generate knowledge about the effectiveness of an intensive behavioral focused program, developed to gain stability of placement for young foster children.

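### Independent t-tests leave age unused in a sample aged 3 to 7 with no adequate baseline, which costs precision but not validity

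*Protocol article*

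**What the plan says.** Inclusion criteria gives one numeric entry condition: "Children are eligible if they are between 3 and 7 years of age and indicated for permanent foster care placement".

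Planned statistical analyses gives the method for continuous outcomes in one sentence: "The continuous measures are analyzed with repeated measures (mixed models) and independent t-tests". It does not say which measure gets which method, and it neither lists nor excludes covariates for the mixed models.

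Data collection separates repeated from single-occasion measures. Of the questionnaires it says: "Parents and teachers are asked to fill out the questionnaires at all six measurements occasions". Of the laboratory session it says: "The Strange Situation Procedure and accompanying VU-AMS measure is scheduled one week before the end of the treatment". Heart rate, respiratory sinus arrhythmia and pre-ejection period therefore have no earlier value.

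The Discussion states: "A second limitation to our RCT is the lack of an adequate baseline measure". Table 2 places T(1) six weeks after the start, so even the first questionnaire comes after allocation. The protection offered is randomisation: "Adhering to a randomized trial will minimize baseline differences between children in the two conditions".

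**The concern.** The t-test compares two means and nothing else. At the upper end of the age band a child is more than twice as old as at the lower end, and both behaviour scores and autonomic measures may vary with age. With no pre-treatment measurement of the outcomes, the analysis cannot use an earlier score to reduce unexplained variation. Age at referral must be known to establish eligibility, so it is available for every child and cannot be affected by treatment.

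Two things are at stake in a trial of 40 per arm. Any variation due to age stays in the error term and widens the confidence intervals. A chance difference in mean age between the arms also stays in the observed treatment difference, where an adjusted model would remove it.

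**Working it through.** **The plan's own figure.** Sample size calculation gives 34 per arm for 40% versus 5% on the Disturbance of Attachment Interview (two-sided 0.05, 90% power, Fisher's exact test), raised to 40 for 10% cross-over. The continuity-corrected two-proportion formula gives 34, and exact Fisher power at 34 is 0.937. With cross-over the MTFC-P rate becomes 0.9 × 0.05 + 0.1 × 0.40 = 0.085. Exact power against 0.40 is then 0.828 at 34 and 0.900 at 40 per arm. The stated figures hold. They rest on a dichotomous outcome and do not depend on how age is handled, so this point changes nothing there.

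**Inputs for the check.** From the article: ages 3 to 7, and 40 per arm. Assumed: entry age uniform, either from 3.0 to just under 8 or from 3.0 to 7.0; correlation r of age with the outcome between 0.2 and 0.5.

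**Validity of the unadjusted test.** In 20,000 simulated trials of 40 versus 40 under simple randomisation, with age explaining 0, 5, 10, 20 and 30% of outcome variance, type I error was 0.048, 0.052, 0.050, 0.048 and 0.051. The mean difference was within 0.003 SD of zero throughout. There is no bias and no excess of false positives.

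**Precision.** Adjustment multiplies the residual variance by 1 − r².
- r = 0.2: reduction 0.04, or 4%; equivalent size 40/0.96 = 41.7, about 42 per arm.
- r = 0.5: reduction 0.25, or 25%; equivalent size 40/0.75 = 53.3, about 53 per arm.

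The standard error shrinks by √0.96 = 0.98 to √0.75 = 0.87, so confidence intervals narrow by about 2 to 13%.

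**Power.** For an assumed standardised difference of 0.5 at 40 per arm, the unadjusted t-test has power 0.60. With adjustment it is 0.62, 0.64, 0.70 and 0.75 if age explains 5, 10, 20 and 30% of the variance.

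**Chance age gap.** SD of age = range/√12, and SE of the difference in mean age = SD × √(2/40).

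| Assumed ages | SD (years) | SE of gap (years) | Chance of a gap over 0.5 year |
|---|---|---|---|
| 3.0 to under 8 | 5/√12 = 1.44 | 0.32 | 12% |
| 3.0 to 7.0 | 4/√12 = 1.15 | 0.26 | 5% |

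A gap of 0.5 year shifts the observed difference by r × 0.5/SD. The lowest value is 0.2 × 0.5/1.44 = 0.07 SD and the highest 0.5 × 0.5/1.15 = 0.22 SD. These shifts average to zero over repeated randomisations, and the t-test's standard error already allows for them. An adjusted model removes them from the realised estimate.

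**The case against.** The best defence is that an unadjusted t-test in a randomised trial is not an error, and this stands. A reader might infer that age differences bias the treatment contrast. The simulation shows otherwise under simple randomisation, so nothing beyond lost precision is claimed. The Randomization section does say that the allocation ratio changes about every six months, which simple 40:40 randomisation does not represent. That is a separate question and is not needed here.

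A reader might also infer that raw sums from the two CBCL forms are pooled, because "The CBCL is completed by foster parents and consists of hundred (ages 1.5-5), respectively 113 (ages 6–18) items", and the TRF likewise has two age versions. A child who moves to the older form during follow-up would then seem to change in behaviour. The article does not support this. It does not say how the forms are scored or combined and never mentions raw sums, and a condensed article commonly leaves such detail to the full protocol or SAP. Form follows age, so both arms face the same expected rate of change. Nor do the t-test and the forms clearly meet: the CBCL and TRF are completed at all six time-points and suit the mixed models, while the single-occasion session uses neither form.

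Finally, the article does not assign the t-test to the autonomic outcomes. The recording covers several episodes, so a repeated-measures model is possible. That is correct, but t-tests are named for continuous measures without restriction, and outcomes taken at one visit are their natural place. Covariates for the mixed models may stand in a fuller document. A t-test cannot take one wherever it is used.

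**Conclusion.** The point holds as one of efficiency. The article names a method that cannot use age, in a sample with a wide age range, no adequate baseline and some outcomes seen once. Under randomisation the method is valid. The loss amounts to 4 to 25% of the residual variance, or about 42 to 53 children per arm against 40, if the correlation of age with outcome lies between 0.2 and 0.5. That range is an assumption; near zero the gain vanishes. The gap probabilities also rest on uniform entry ages. The eligibility sentence contains no error, the Discussion discloses the missing baseline openly, and the sample size is unaffected.

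**What to change.** In Planned statistical analyses, replace the independent t-tests with a linear model of outcome on arm plus age at referral. Include age at referral as a covariate in the mixed models. Keep the unadjusted t-test as a sensitivity analysis. Fix this before outcomes are compared by arm; Status of the trial reports that inclusion is still in progress. No new data are needed, since age is already established for eligibility. The cost is a change of wording and one degree of freedom per model.

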### Exclusion criteria

Children are excluded if they do not meet the inclusion criteria and when foster parents provide no informed consent. When children’s legal authorities provide no informed consent or when foster parents disagree with the treatment they are assigned to, the children are excluded from the randomized trial.

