### Sample size calculation

Sample size is calculated based on the DAI (see Measures). The DAI is a dichotomous measure reflecting symptoms of disturbed attachment (1 = not or somewhat present, 2 = definitely present). From cross-sectional data it is known that the prevalence of symptoms of disturbed attachment in comparable populations is approximately 40% [39]. Based on unpublished pilot data, which also suggested 40% of participants would be symptomatic at any time-point in the TAU intervention, we expect that in the present randomized controlled trial (RCT), a 40% level of symptomatic individuals will be maintained until the end of the TAU. Based on Fisher and Kim’s study [24], which reported increased secure attachment behavior (behavior that is incompatible with disturbed attachment) after MTFC-P, we expect a decline of disturbed attachment over the course of the MTFC-P. The aim is to reduce the proportion of children with symptoms of disturbed attachment to 5% at the end of MTFC-P. Including 34 children in both conditions can statistically reveal a difference between conditions with 90% power, using Fisher's exact test with a 0.05 two-sided significance level for analysis. The study was initially planned as a ‘normal’ pre-randomization trial. However, we observed low recruitment of participants because children arrive in a crisis situation and obtaining consent from biological parents was problematic (see below, Randomization). We therefore changed to a pre-randomization with single consent method to allow the birth parents enough time to decide on their participation. Parents of children randomized to MTFC-P who refused consent received TAU after randomization. We expected a 10% cross-over rate. This cross-over rate reduces the efficiency of the trial by 19% and requires a 20% addition to the sample size [52]. We therefore augmented the planned sample size from 34 to 40 per treatment arm (under 90% power) to counter the dilution effects by the cross-overs in the intention-to-treat analysis and to diminish the type II error probability.

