#### Randomization

Random allocation to either condition is needed to reduce selection bias and to be able to attribute effects to MTFC-P or TAU. However, referral to foster care is often made in crisis and immediate start of care is a prerequisite. The start of foster care is also usually accompanied by resistance or absence of the biological parent (the child’s legal authority) or a vacuum in authority. We expect this brief time interval between referral and start of the intervention, together with inaccessibility of a legal authority, to hamper random allocations. Following conventional randomization, researchers are unable to ensure that the child’s legal authority has retrieved, understood and signed informed consent before the child must be allocated to a treatment [53]. This results in a preliminary loss of participants. A pre-randomization trial, wherein randomization is determined prior to informed consent [54], is implemented as this promotes the inclusion of participants by extending the time period between referral and start of treatment. Researchers then have more time to obtain informed consent, avoiding preliminary dropout [55]. An independent researcher makes a random allocation list, varying per time period. Distribution of assignment to both conditions varies over time periods (approximately every six months), based on available treatment places. This is necessary to guarantee that children receive immediate treatment and are not placed on a wait list. Conditions are disclosed to the treatment team and participants immediately after referral. If legal authorities will not sign informed consent, children receive TAU. The condition is not disclosed to any members of the research team concerned with coding data.

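### Refusers are excluded after randomisation in one section but kept as intention-to-treat cross-overs in others, so the primary analysis set needs reconciling

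*Protocol article*

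**What the plan says.** Under Randomization, the protocol article describes a pre-randomisation design: the arm is fixed before consent is sought and is made known to the treatment team and participants straight after referral. Refusal is therefore an event after randomisation, decided by people who know the arm.

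The article then gives these statements about children affected by refusal:

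- **Exclusion criteria:** "legal authorities provide no informed consent or when foster parents disagree with the treatment they are assigned to, the children are excluded". What they are excluded from is the randomised trial itself. The rule covers two groups: children whose legal authority gives no consent, and children whose foster parents reject the assigned arm.
- **Sample size calculation:** "Parents of children randomized to MTFC-P who refused consent received TAU after randomization". This section expects 10% cross-over and raises the sample from 34 to 40 per arm to offset the resulting dilution of the intention-to-treat comparison.
- **Randomization:** "If legal authorities will not sign informed consent, children receive TAU".
- **Data collection, Table 2, footnote to the consent row:** no consent, "child randomized to treatment as usual".
- **Planned statistical analyses:** "Primary analyses are performed following the intention-to-treat principle". A treatment-received analysis is added, and so is a separate comparison of the refusers who had been allocated to MTFC-P and then received TAU.

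The Discussion adds that people who refuse one of the treatments would be left out of a conventional trial, and it names cross-over as the price of the Zelen design.

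**The concern.** A child whose legal authority refuses cannot be both outside the randomised trial and a cross-over within its intention-to-treat analysis. The Exclusion criteria apply the very exclusion that the Discussion contrasts with this design.

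The choice affects validity. Under the Sample size and Randomization sections, refusal changes treatment in one direction only: a child allocated to TAU without consent still receives TAU. Loss through refusal therefore cannot be assumed to balance between arms. Removing such children leaves groups that are no longer the randomised ones. The Discussion concedes that there is no adequate baseline measure and relies on randomisation to limit differences between arms, so an imbalance from selective exclusion would be hard to detect or adjust for.

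The second group, children whose foster parents reject the arm, raises the same problem of principle. Their exclusion also follows disclosure and depends on the arm.

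**Working it through.** **1. Inputs from Sample size calculation.** TAU rate 40% ("a 40% level of symptomatic individuals will be maintained until the end of the TAU"); MTFC-P rate 5%; Fisher's "exact test with a 0.05 two-sided significance level for analysis"; 10% cross-over; "Including 34 children in both conditions can statistically reveal a difference between conditions with 90% power".

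**2. Reproducing 34 per arm.** Mean rate (0.40 + 0.05)/2 = 0.225; difference 0.35.
- Uncorrected: n′ = [1.960·√(2 × 0.225 × 0.775) + 1.282·√(0.40 × 0.60 + 0.05 × 0.95)]² / 0.35² = 27.8, so 28.
- With continuity correction: n = (n′/4)·[1 + √(1 + 4/(n′ × 0.35))]² = 33.2, so 34.

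This matches the stated figure. Exact Fisher power by full enumeration is 0.937 at 34 per arm and already 0.907 at 31 per arm.

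**3. Reproducing the increase to 40.** Efficiency is (1 − 0.10)² = 0.81, the stated 19% loss. A 20% addition gives 34 × 1.20 = 40.8; dividing by 0.81 gives 42.0. The stated 40 is close to both.

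**4. Which reading the 40 belongs to.**
- *Refusers kept in the MTFC-P arm.* The MTFC-P rate becomes 0.90 × 0.05 + 0.10 × 0.40 = 0.085. Exact Fisher power for 40% v 8.5% is 0.828 at 34 per arm and 0.900 at 40 per arm. The increase does what it is meant to do.
- *Refusers excluded.* There is no dilution and the rates stay at 40% v 5%. With 34 allocated per arm, 34 × 0.90 = 30.6, about 31, would remain in MTFC-P, and even 31 in both arms gives 0.907. With 40 allocated, 40 v 36 gives a nominal 0.971, but for groups that are no longer as randomised.

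So the sample size assumes that refusers stay in their allocated arm, which the Exclusion criteria do not allow.

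**5. Possible bias from exclusion.** Assumptions, none of which the article supplies except the 40% and the 10%: no treatment effect, 40% symptomatic overall, 10% refusing in the MTFC-P arm only, and a fraction q of refusers symptomatic. The remaining MTFC-P rate is (0.40 − 0.10q)/0.90, compared with 40% in TAU. The last column is the exact Fisher rejection probability at 40 v 36.

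| q | MTFC-P rate after exclusion | Spurious difference | Rejection probability |
|---|---|---|---|
| 40% | 40.0% | 0 | 0.036 |
| 50% | 38.9% | 1.1 points for MTFC-P | 0.037 |
| 60% | 37.8% | 2.2 points for MTFC-P | 0.040 |
| 70% | 36.7% | 3.3 points for MTFC-P | 0.045 |
| 80% | 35.6% | 4.4 points for MTFC-P | 0.051 |

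The sign reverses below 40%. At q = 30%, (0.40 − 0.03)/0.90 = 41.1%, which is 1.1 points against MTFC-P.

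**The case against.** The best defence is that the Sample size, Planned statistical analyses and Discussion sections together form one coherent plan: refusers take TAU, intention-to-treat is primary, two supplementary analyses are added, and the sample is enlarged. A reader might infer from the conflict that intention-to-treat cannot be carried out at all. That goes too far. It is feasible under those sections and fails only if the Exclusion criteria are applied.

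Two other strong readings also lack support.
- A reader might infer that other sections treat foster parents who reject the arm as cross-overs. They do not say so. Sample size calculation concerns birth parents, Randomization concerns legal authorities, and Planned statistical analyses speaks of parents. Only the Discussion refers generally to participants who refuse. For these carers the objection is to exclusion after disclosure, not to an explicit contradiction.
- A reader might take the Table 2 footnote as a third analysis set with refusers counted as TAU. It annotates a procedural table and does not mention analysis. It may loosely restate that such children receive TAU. Planned statistical analyses describes the refusers as randomised to MTFC-P, which preserves their allocation. The footnote is ambiguous wording that could be misread, no more.

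The Exclusion criteria might also mean refusal of research data while the Sample size section means refusal of treatment. The article never separates the two, and children whose data may not be used would still be randomised children with missing outcomes. Nor does condensation into an article explain the conflict: these are opposing statements, not an omission.

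Finally, the bias at the planned refusal rate is modest beside the planned difference of 40 − 5 = 35 points. That stands, and it limits the size of the point without removing it.

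**Conclusion.** The point holds for the analysis set. For children whose legal authority refuses, the Exclusion criteria contradict the Sample size, Randomization and Planned statistical analyses sections. For children whose foster parents reject the arm, the exclusion conflicts with the intention-to-treat principle without being contradicted outright. The sample-size arithmetic is sound and shows which reading was intended.

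At 10% refusal the spurious difference from exclusion is about 1 to 4 points in favour of MTFC-P for symptomatic rates of 50% to 80% among refusers. It is nil or in the opposite direction for other rates, so no direction of bias can be asserted. The refuser rates and the one-arm refusal are assumptions. The matter still needs correcting because it leaves open, on the face of the document, who is in the primary analysis.

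**What to change.** 1. Reconcile the Exclusion criteria with the Sample size, Randomization and Planned statistical analyses sections: remove refusal of consent, and refusal of the allocated arm, as grounds for leaving the analysis set.
2. State that every eligible randomised child is analysed in the arm allocated, whatever treatment was received.
3. Reword the Table 2 footnote so that it describes treatment received and not allocation.
4. Where data may not be used, or were not collected, for lack of consent, count the child by arm as randomised with missing outcome. Do not label the resulting analysis full intention-to-treat.

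The cost is wording and reporting, with no extra participants. The intention-to-treat effect may be slightly smaller than one computed without refusers. Recruitment began in mid-2009, so if the exclusion has already been applied, outcomes not collected for those children cannot be recovered. Their number by arm should then be reported.
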